### Secondary objectives are

Secondary safety outcomes are: Serious Adverse Events (SAEs) and Adverse Events (AEs);

GPS; KS; Progression-free survival (PFS) at the end of the study; Overall compliance; Percentage of patients eligible from total number recruited; Response evaluation criteria in solid tumours (RECIST) data (if available).

**The following outcomes will be measured in this study, for use in planning the main study, at the following time points: **screening visit, week 1, 3, 6, 9, 12, 16 and 20 weeks after intervention commencement.

Secondary measured outcomes: Lean body mass assessed by bioelectrical impedance analysis (Tanita BC-418 Segmental Body Composition Analyzer, Tanita); QoL and fatigue assessed by the following questionnaires MFSI-SF, FAACT, and WHOQOL-BREF; Serum levels of proinflammatory 'classic cachexia cytokines' (IL-1, IL-6 and TNF-α) measured by Bio-Plex Pro assay, Bio-Rad); Hand grip strength assessed by hand grip dynamometry of the dominant hand, the average of three attempts with 1 minute rest between attempts (Jamar); Leg grip strength assessed by back/leg dynamometry of the right leg, the average of three attempts with a 1 minute rest between attempts (PE018 Back Dynamometer, Access Health).

Secondary measured outcome MRI thigh skeletal muscle values as assessed 'blinded' by University of Auckland and Auckland District Health Board MRI departments. Scans will be performed at screening visit and week 20 after intervention commencement only.

### Randomisation and standardised treatment scheme

All patients enrolled will be identifiable throughout the study. The investigator will maintain a personal list of patient numbers and patient names. Upon consent each patient will receive a unique identification number. After the patient's eligibility for randomisation has been assessed he/she will be randomly assigned to one of the two treatment arms in a 1: 2 ratio (EPA and celecoxib vs. EPA and celecoxib, PRT and EAA).

### Treatment scheme

Both study arms receive for a period of 20 weeks; 2.09 g EPA Ethical Nutrients Hi-Strength Liquid Fish Oil oral liquid (fruit punch flavour), 5.5 mls per day and 300 mg per day of celecoxib.

### Experimental group

Additionally, patients in the experimental group undergo two sessions a week for 20 weeks of a tailored PRT programme under the supervision of a trained exercise therapist. All PRT sessions will be carried out at North Shore Hospice. There will be a 5-10 minute warm up, followed by the exercise prescription, and a 5 minute cool-down. 20 g of essential amino acids high in leucine will be administered to the patients 1 hour after PRT.

All patients are invited to continue with compassionate use after the end of the study.

### Evaluation and follow-up

All patients must have appropriate laboratory analysis and MRI study conducted prior to study enrolment to meet eligibility criteria. Laboratory parameters will be obtained three weekly. The patient will be asked at each visit for any adverse event (SAE and AE) as well as concomitant medication. QoL questionnaire (MFSI-SF, FAACT and WHOQOL-BREF) will be handed out to all patients on screening visit, weeks 1, 3, 6, 9, 12, 16 and 20.

Patients can withdraw from study participation at any time. Patients will be taken off the study if unacceptable toxicity appears. Unacceptable toxicity is defined as serious side effect or irreversible grade 3 toxicity. After the individual ending of the study subjects will receive the best available medical and nutritional care. Patients will undergo MRI at the beginning and at the end of study. Patients will be tracked and followed up until death.

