### Statistical consideration

The intent-to-treat population including all patients who are randomised with study medication assignment designated according to initial randomisation, regardless of whether patients receive study medication or receive a different medication from that to which they were randomised. This will be the primary population for evaluating the acceptability, and measured outcome endpoints. The safety population consisting of all patients who received at least one dose of study medication or treatment.

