### Primary analysis

This will be assessed by the summary of a patient-rated Likert scored questionnaire asking 10 questions on the acceptability of the above multi targeted approach, both at week12/visit 5 and end of study visit. Medians and ranges will be estimated.

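### Removal for toxicity is written as leaving the study, not only stopping treatment, so acceptability ratings and late measures may be missing for patients who could not tolerate the regimen

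*Protocol article*

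**What the plan says.** Evaluation and follow-up sets the removal rule: "Patients will be taken off the study if unacceptable toxicity appears". The trigger follows: "Unacceptable toxicity is defined as serious side effect or irreversible grade 3 toxicity". The next sentence treats this as the end of the study for that patient: "After the individual ending of the study subjects will receive the best available medical and nutritional care". The same paragraph closes with "Patients will be tracked and followed up until death", without naming any outcome or visit that this covers.

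Statistical consideration defines the intent-to-treat population as everyone randomised, "regardless of whether patients receive study medication or receive a different medication from that to which they were randomised", and adds: "This will be the primary population for evaluating the acceptability, and measured outcome endpoints".

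Primary analysis places the ten-item acceptability questionnaire "both at week12/visit 5 and end of study visit" and gives the summary: "Medians and ranges will be estimated". The article does not say whether the end of study visit is week 20 or the patient's own last visit.

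The measured outcomes are scheduled at screening and weeks 1, 3, 6, 9, 12, 16 and 20 (Secondary objectives). Adverse events are asked about at each visit (Evaluation and follow-up).

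**The concern.** The primary population is chosen so that stopping treatment does not remove a patient from the evaluation. The removal rule, as worded, takes a patient out of the study at the moment treatment fails on tolerability. These are the patients for whom an intent-to-treat summary and an on-treatment summary differ.

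The primary endpoint is whether patients find the regimen acceptable. A patient removed for toxicity could well give one of the lowest ratings, and a removal before week 12 takes away the week-12 rating. Three further aims are affected:

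- **Planning data.** The mixed models are meant to supply variances, covariances and time trends for the main study. Late visits would be observed mainly in patients who tolerated the regimen.
- **Safety.** If visits end, adverse events after exit are no longer elicited by the planned route.
- **Retention.** This is a stated feasibility aim (Study rationale/purpose). Removal by rule and loss of the patient's willingness to attend would be counted together.

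**Working it through.** **1. The plan's own figure.** The article gives 21 patients allocated 1:2. 21 × 1/3 = 7 control and 21 × 2/3 = 14 experimental; 7 + 14 = 21, so the split reproduces. The article gives no alpha, power, effect size, dropout rate or toxicity rate, so no sample-size figure depends on this point.

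**2. Does the text mean study or treatment?** The sentence before the rule concerns a patient's withdrawal from participation. The sentences after it give the toxicity trigger and then speak of an individual ending of the study with a handover to other care. Where the article means treatment, as in Statistical consideration, it uses the term study medication. The plain reading is therefore that toxicity ends participation. No section says that scheduled assessments continue afterwards, and none says explicitly that they stop.

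**3. What one exit loses on that reading.** There are eight time points for the measured outcomes. Take an exit between weeks 6 and 9 as an example:

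- Kept: screening and weeks 1, 3 and 6 (4 of 8).
- Lost: weeks 9, 12, 16 and 20 (4 of 8), and the week-12 acceptability questionnaire.
- Unclear: the end-of-study questionnaire, because that visit is not defined.
- Unclear: the closing MRI. Evaluation and follow-up puts it at the end of study; Secondary objectives fixes it at week 20 only.

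**4. Weight of one exit.** 1/14 = 7% of the experimental arm; 1/7 = 14% of control.

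**5. How likely is an exit?** With an assumed removal rate p, independent between patients, P(at least one of 14) = 1 − (1 − p)^14. P(at least three) is the matching binomial tail.

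| Assumed p | Expected removals, 14p | P(≥1 of 14) | P(≥3 of 14) |
|---|---|---|---|
| 5% | 0.7 | 0.51 | 0.03 |
| 10% | 1.4 | 0.77 | 0.16 |
| 20% | 2.8 | 0.96 | 0.55 |
| 30% | 4.2 | 0.99 | 0.84 |

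**6. Effect on medians and ranges (invented scores).** Start with 14 ratings on a 1-to-5 scale: 5, 5, 5, 4, 4, 4, 4, 4, 3, 3, 3, 3, 2, 2. Suppose the last k patients are removed and would have rated 1.

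| k | Observed only: median (range) | All 14: median (range) |
|---|---|---|
| 1 | 4 (2–5) | 4 (1–5) |
| 2 | 4 (3–5) | 4 (1–5) |
| 3 | 4 (3–5) | 4 (1–5) |
| 4 | 4 (3–5) | 4 (1–5) |

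In this example the median does not move, but the bottom of the range rises from 1 to 2 or 3. The loss hides the worst ratings more than it shifts the centre. The scores only illustrate the mechanism.

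**The case against.** A reader might infer that all outcome data stop at a toxicity exit and that the intent-to-treat analysis therefore cannot be delivered. The documents do not support that much.

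- The intent-to-treat definition says who is included and under which arm. It does not promise complete data, so it is not literally contradicted. Removed patients stay in the population with the data they have, and stay in the safety population after one dose.
- Patients are followed until death, so at least vital status is kept. The end-of-study questionnaire, and perhaps the MRI, might be done at an individual exit visit, although the week-20 timing in Secondary objectives speaks against this for the MRI.
- Mixed models use every visit before exit, so this is not a completers-only analysis. Their main purpose here is planning estimates, and the primary endpoint has no planned between-group test.
- Nothing supports a particular number of exits. The celecoxib studies cited in the background reported no adverse events in one randomised study of eleven patients and no grade 3 or 4 toxicity in another of twenty-four. They are small and do not cover the full regimen, but they do not point to a high rate.
- A condensed article may leave the handling of early exits to the full protocol.

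The first four points stand and limit the size of the problem. The last does not remove it: the article does not merely omit detail but states a rule which, followed as written, leads to missing outcomes. Nor do the mixed models fully answer it. Their stated terms are group, time and the interaction, so missingness driven by toxicity is handled only as far as a patient's earlier outcomes predict it. They also do nothing for the acceptability questionnaire, which is summarised by medians and ranges.

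**Conclusion.** The point holds as a conflict of purpose between two stated rules. The article merges stopping treatment with leaving the study, while its primary population needs outcomes from patients whatever they received. The main consequence is for the primary endpoint: on the plain reading, a patient removed before week 12 gives no week-12 acceptability rating. Late-visit estimates and adverse-event reporting are affected to a lesser degree.

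One removal costs 7% of the experimental arm or 14% of control. At least one removal among the 14 is more likely than not across the assumed range of 5% to 30% (0.51 to 0.99); a rate below 5% would lower that figure. Three or more ranges from unlikely (0.03) to likely (0.84) over the same range and should not be taken as expected.

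The conclusion rests on the plain reading of the removal rule and on the assumed rates. The change is worth making before recruitment, but no test or sample-size figure depends on it.

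**What to change.** Reconcile Evaluation and follow-up, Statistical consideration and Primary analysis on data collection only:

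1. State that meeting the toxicity definition ends study treatment but does not by itself end data collection. Patients who are willing, and for whom the investigator judges the assessment suitable, continue the assessments already planned. The acceptability questionnaire and adverse events come first.
2. Define the end of study visit as either week 20 or the individual's last visit, and align the timing of the MRI with it.
3. Say what follow-up until death collects.
4. Record treatment discontinuation and withdrawal from the study as two separate variables, each with date and reason, so that retention can be reported apart from tolerability.

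The criterion for stopping treatment is left as it is. The cost is a few sentences of protocol text and an added case-report field; the visits are already scheduled. The downside is that some patients who stop treatment will decline further visits, so some data will still be missing, but the reason will then be recorded.

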### Statistical consideration

The intent-to-treat population including all patients who are randomised with study medication assignment designated according to initial randomisation, regardless of whether patients receive study medication or receive a different medication from that to which they were randomised. This will be the primary population for evaluating the acceptability, and measured outcome endpoints. The safety population consisting of all patients who received at least one dose of study medication or treatment.

### Primary analysis

This will be assessed by the summary of a patient-rated Likert scored questionnaire asking 10 questions on the acceptability of the above multi targeted approach, both at week12/visit 5 and end of study visit. Medians and ranges will be estimated.

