**Methods/Design:**

Auckland's Cancer Cachexia evaluating Resistance Training (ACCeRT) is an open label, prospective, randomised controlled feasibility study with two parallel arms. All patients will be treated with EPA and the COX-2 inhibitor celecoxib on an outpatient basis at the study site. In the experimental group patients will participate in PRT twice a week, followed by the ingestion of essential amino acids high in leucine. A total of 21 patients are planned to be enrolled. Patients will be randomised using 1:2 ratio with 7 patients enrolled into the control arm, and 14 patients into the treatment arm. The primary endpoint is the acceptability of the above multi-targeted approach, determined by an acceptability questionnaire.

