### Study objectives

The primary objective of this clinical trial is to evaluate whether a multi-targeted approach encompassing resistance training element is acceptable for lung cancer patients experiencing cancer cachexia. This will be assessed by the analysis of a patient-rated Likert scored questionnaire asking 10 questions on the acceptability of the above multi targeted approach, both at week12/visit 5 and end of study visit.

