### Eligibility criteria

#### Inclusion criteria

**1**. Patients ≥ 18 years old

**2**. Histological confirmed non-small cell carcinoma of the lung. Histological or cytological specimens must be collected via surgical biopsy, brushing, washing or core needle aspiration of a defined lesion. Sputum cytology is not acceptable

**3**. Patients should be aware of the diagnosis of cancer

**4**. Patients able to give written informed consent obtained according to local guidelines

**5**. Karnofsky Score (KS) ≥ 60 or ECOG Performance Status 0,1, 2 or 3

**6**. Recently completed first-line platinum-based chemotherapy (minimum of 1 month post last cycle)

**7**. Life expectancy ≥ 20 weeks

**8**. Fulfils the following 'cachectic definition'

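### Acceptability is first scored at week 12 and then at an undefined end of study visit, so the primary medians may miss patients who left early because they rejected the programme

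*Protocol article*

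**What the plan says.** The abstract of the protocol article (Methods/Design) makes a questionnaire the sole basis of the primary endpoint: "The primary endpoint is the acceptability of the above multi-targeted approach, determined by an acceptability questionnaire". Study objectives and Primary analysis give the same two times, "both at week12/visit 5 and end of study visit". The summary is brief: "Medians and ranges will be estimated".

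Statistical consideration defines the analysis set, "The intent-to-treat population including all patients who are randomised", and adds: "This will be the primary population for evaluating the acceptability, and measured outcome endpoints".

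Evaluation and follow-up states: "Patients can withdraw from study participation at any time". It also provides for removal because of unacceptable toxicity. Under Experimental group, resistance training runs twice weekly for 20 weeks. The required prognosis is of the same length: "Life expectancy ≥ 20 weeks" (Inclusion criteria).

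The article does not define the end of study visit, tie the questionnaire to withdrawal, or give a value or category to a patient without one.

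**The concern.** A median can use only scores that exist. Naming all randomised patients as the population does not create a score for someone who left before the questionnaire was first given. The stated population and the measurement schedule therefore do not fit together for early leavers.

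For most endpoints, dropout hides the outcome. Here, leaving because the programme is intolerable is itself strong evidence about the outcome. If the first reading is at week 12, the people asked have already tolerated 12 of the 20 weeks. At stake is whether the primary result of a feasibility study can register the rejection it is meant to detect.

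**Working it through.** **The plan's own figure.** The only sample-size figure is 21 patients split 1:2. This reproduces: 21/3 = 7 control and 2 × 21/3 = 14 experimental. No dropout rate, acceptability cut-off or scale length is given, so the size of the effect cannot be derived from the document. What follows is illustrative.

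**Step 1: who can have a score.**

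| Time of leaving | Week 12 score | End of study score |
|---|---|---|
| Before week 12 | No | Only if that visit is also an exit visit |
| Between week 12 and week 20 | Yes | Only if that visit is also an exit visit |
| Completes 20 weeks | Yes | Yes |

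The gap concerns the first row: patients who may contribute nothing at all.

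**Step 2: how the summary responds.** Assumptions, not from the document: a 1-5 scale; completers split as evenly as possible between 4 and 5; q patients quit before week 12 without a questionnaire; quitters are counted as 1; a score of 4 or 5 means acceptable. The experimental arm has n = 14. The returned median uses 14 − q scores, and the all-randomised median adds q scores of 1. The share acceptable is 100% of responders throughout, against (14 − q)/14 of those randomised.

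| q | Returned median (range) | All-randomised median (range) | Share of all 14 acceptable |
|---|---|---|---|
| 0 | 4.5 (4-5) | 4.5 (4-5) | 14/14 = 100% |
| 4 | 4.5 (4-5) | 4 (1-5) | 10/14 = 71% |
| 6 | 4.5 (4-5) | 4 (1-5) | 8/14 = 57% |
| 7 | 5 (4-5) | 2.5 (1-5) | 7/14 = 50% |
| 8 | 4.5 (4-5) | 1 (1-5) | 6/14 = 43% |

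Neither the returned median nor its range reacts to quitting.

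The median over all 14 is also slow to react. It stays at 4 up to q = 6, because the 7th and 8th ordered values are still completers' scores. From q = 8 it equals whatever value quitters are assigned. Putting a low score into the median is therefore not enough, and counts are needed beside it.

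**Step 3: how easily several early leavers arise.** If each of 14 patients independently leaves before week 12 with probability p, then P(at least 4 leave) = 1 − Σ(k = 0 to 3) C(14,k) p^k (1 − p)^(14 − k). For p = 0.2 this is 1 − (0.044 + 0.154 + 0.250 + 0.250) = 0.302.

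| p (assumed) | 10% | 20% | 30% | 40% | 50% |
|---|---|---|---|---|---|
| P(at least 4 of 14 leave) | 4% | 30% | 65% | 88% | 97% |

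**Step 4: is earlier collection practical?** Evaluation and follow-up has the quality-of-life forms handed out at screening and on four occasions before week 12 (weeks 1, 3, 6 and 9). Contact with patients early in the programme is already planned.

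**The case against.** The strongest reply concerns the term end of study visit. The article never equates it with week 20. Evaluation and follow-up, just after describing withdrawal and toxicity removal, speaks of an ending that is particular to each patient. On that reading a leaver answers the 10 questions on exit and the gap largely closes. The reading is possible, but the text does not state it, and a patient who withdraws may not attend. One clarifying sentence is still needed.

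A second reply is that a journal article leaves missing-data rules to the full protocol or analysis plan. That is fair for rules, and their absence is not the point here. The point is what the article fixes: a questionnaire-only endpoint, two times of which the first is week 12, medians, and an intent-to-treat label. An answer never sought at exit cannot be recovered by a later analysis rule.

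A reader might go further and infer three things that the document does not support:

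- **That this is a completers' analysis.** No text restricts it so, and a patient leaving after week 12 still gives a week 12 score.
- **That the questionnaire median alone decides whether a full study follows.** Study rationale/purpose also lists recruitment, retention and safety, and the secondary objectives include compliance and adverse events. Early leaving will be visible to the study, though not in its primary result.
- **That losses will be large and acceptability is certainly overstated.** The life-expectancy criterion makes loss plausible but gives no rate. Death and progression are not rejection of the programme, and the direction of any bias from such losses is unknown.

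**Conclusion.** The concern holds in a limited form. As written, a patient who leaves before week 12 because the programme is unacceptable or toxic contributes no acceptability score unless the end of study visit doubles as an exit visit. The intent-to-treat label does not cure this.

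The size cannot be stated. In the illustration the returned median stays at 4.5-5 for 0 to 8 quitters of 14, while the all-randomised median goes from 4.5 to 1. The value of 1 rests on giving every quitter the lowest score. If leavers would have scored like completers, there would be no distortion. What does not depend on that choice is that the planned summary contains no information from leavers without a questionnaire.

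Replacing the medians with a single acceptable/not acceptable measure is not required. The article sets no cut-off, and patients too ill to attend would be scored as rejecting the programme.

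**What to change.** 1. State that the same 10 questions, with the reason for leaving, are given at any early exit, and that this counts as the end of study visit.
2. Keep the medians and ranges, and give the number of patients who answered.
3. Beside them, account for all 14 patients randomised to the experimental arm:
   - the number who stayed and rated the programme acceptable, with the cut-off set in advance;
   - the number who left for programme-related reasons or toxicity, counted as not acceptable;
   - the number lost to death, progression or illness, shown separately, with the result given both with and without them counted as not acceptable.

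The cost is some added wording and one extra use of an existing questionnaire. No further patients are needed. The reported acceptability may turn out less favourable.
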